**Data collection**

*Patient / Family Carer Measures (Baseline and three month follow up)*

We will be keeping careful records about eligible referrals, consent, and adherence to intervention as these are the primary measures of feasibility and acceptability.

We will collect all interview data from the carer to reduce patient burden and to ensure that data is comparable if the degree of impairment of the patient prevents them completing the questionnaires (interview time: expected to be about 50 minutes). We will inform feasibility and test procedures by collecting validated clinical and cost effectiveness measures planned for a full trial. We will also, as the HTA requests, ask study participants to consent to long-term follow-up beyond the study using routinely collected data from GP, electronic mental health service notes and DCRIS databases.

Patient: Baseline only

1. Socio-demographic details for the included participants with dementia: age, sex, current marital status, ethnicity, level of education, last occupation (baseline only).
2. Medication- psychotropic medication at baseline and at three months (for three months) to delineate the role of rescue medication (incorporated in CSRI below).
3. Dementia- type diagnosed (from referral)
4. Severity of dementia (Clinical Dementia Rating; CDR ^20^). The CDR has six domains: Memory, Orientation, Judgment and Problem solving, Community Affairs, Home and Hobbies, and Personal Care. It is widely used to assess dementia severity through informants.

Patient: Baseline and three months

1. Sleep Disorders Inventory^18^ is validated for measuring sleep disorder in people with dementia and describes the frequency and severity of sleep-disturbed behaviours
2. Actigraphy (baseline and 3 months)
3. Neuropsychiatric symptoms (Neuropsychiatric Inventory)^21^, a validated instrument with 12 domains, which will be included as a secondary outcome in the main trial . This will enable assessment and consideration of whether other neuropsychiatric symptoms, for example, depression and anxiety, or total neuropsychiatric symptoms, may be changed by the intervention.
4. Epworth sleepiness scale (daytime sleepiness)^22^ to assess changes in excessive daytime somnolence. This is an eight item measure assessing tendency to sleep/doze in specific daily situations (possible score range 0-24; a score of >10 indicating excessive sleepiness).
5. DEMQOL proxy ^23^ is a 31 item interviewer-administered questionnaire answered by a carer. It is responsive, valid and reliable measures of quality of life in people with dementia. They have psychometric properties at least as good as other dementia-specific quality of life instruments^24^ and have been used to generate utility values^25^ .
6. Patient services use (CSRI)^17^ is widely used for dementia trials and will delineate treatment as usual (TAU) as well as treatment for those in the active arm of the study and together with the DEMQOL proxy can be used for cost effectiveness^26^.
7. Side effects measure for fall and comorbidities at baseline and follow up. Using a Safety, and Tolerability Assessment to record the occurrence of falls, dizziness, headaches and gastrointestinal symptoms (appetite or bowel symptoms) and any other side effects and whether these were mild, moderate or severe

Carer: baseline and 3 months

1. Socio-demographic details for the carer: age, sex, relationship to patient, co-residency or if not how often sees patient, ethnicity, last or current occupation (baseline only).
2. We will administer two questionnaires for sleep quality to consider which of these is better in this population
   - 1. Pittsburgh Sleep Quality Index: (PSQI)^27^ a validated, reliable instrument to measure the effect on carer sleep (since it is commonly disrupted by sleep-wake patterning of the person with dementia
     2. Sleep Condition Indicator (SCI)^28^ a new eight item scale developed in the UK with date on tens of thousands of people of all ages, and characterises sleep both dimensionally (like PSQI) but also against insomnia disorder criteria (which PSQI does not).
3. The hospital anxiety and depression scale (HADS) ^29^ is a validated , reliable measure to measure mood in carers throughout the age groups
4. Zarit^30^ the most commonly used and well validated measure of burden for carers of people with dementia to indicate whether burden may be changed by the intervention
5. Carer HSQ^31;32^ a 12 item health-related quality of life scale validated throughout the age group and together with CSRI be used for cost effectiveness.

*Power calculation*

With 40 intervention participants (larger to allow a more precise estimate of proportion adhering to intervention) and 20 controls we will achieve the following 95% confidence intervals (CI) for our expected adherence and participation estimates:

1 Proportion of participants adhering to intervention- expected value 75%, 95% CI: 59-87%

2 Proportion of appropriate referrals consenting to the trial-expected value 50%, 95% CI:41-59%

We judge that these confidence intervals provide acceptable ranges to inform continuation to the main trial. Overall we expect that our “stop-go” measures would be related to the proportion adhering-

1. >=70% - go to main trial
2. 60-69 –consider a modified trial design to increase adherence
3. <60 do not progress to main trial using this model.

This sample size will also be sufficient to estimate the standard deviation required for the sample size calculation in the main trial^33;34^.

We estimate that recruitment referral rate will be approximately six potential participants per week; two participants will be suitable and will agree to participate (one per research assistant); and follow-up will be approximately 80%.

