
*Treatment as usual*

*Purpose of treatment as usual arm*

We are comparing the new treatment with treatment as usual (TAU) by itself and participants randomised to the new treatment will also receive usual care. The purpose of a treatment as usual arm is to judge acceptability of being randomised, so that we know the feasibility of moving to a full scale trial. In the START trial many of the prospective participants did not agree to take part in the study 181/472 (38%). We did not ask for a reason to refuse to enter the study but many said it was because of randomisation. Of those who did agree to the study, 4/87 (5%) in the TAU group withdrew because they wanted to be in the active treatment group. We are unclear how these figures will translate to this study and wish to test this, although we judge that many people will wish to be in the active plus TAU arm rather than the TAU arm.

*Content of treatment as usual arm*

We will use the Client services Receipt Inventory^17^ to delineate treatment as usual as we have in other studies. We expect it to vary between trusts and also according to individual patient needs but will incorporate the NICE pathways guidelines for dementia. Services are based around the person with dementia. Treatment is medical, psychological and social. Thus, it consists of assessment, diagnosis, risk assessment and information. These include referral to dementia navigators, medication for Alzheimer's disease or dementia with Lewy bodies, cognitive stimulation therapy, START (in some trusts), practical support (social services provided); risk plans, for example telecare, driving information to the Driver and Vehicle Registry Agency (DVLA), medical identification (ID) bracelets, advice regarding power of attorney and capacity assessment; and social services referral for personal care, day centre and financial advice, treatment of neuropsychiatric symptoms and carer support.

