**Assessment**

*Procedures*

Referrals and recruitment procedure

Prospective eligible participants will be initially approached by a clinician they know and given (or sent) an information sheet or will volunteer through Join Dementia Research. Some prospective participants may have agreed to be contacted for research (as trusts may have a register) but we will still approach a clinician initially to ensure there have been no changes and ask, if possible, if they can make contact. Our experience is that this group of patients may not remember consenting and be very cautious of calls from strangers. Those interested in participating will be referred to the research team. The referral will give the name, sex and relationship of the patient and carer (this will allow testing for external validity by comparing the sample recruited with those who were referred but refused recruitment). The team that is to carry out blinded assessments will telephone them 24 hours or more after they receive the information sheet. They will answer any questions and then arrange to meet those who thought they wished to take part, to obtain their informed consent and complete the baseline assessment before randomisation.

Randomisation

We will use a randomisation list produced by the statistician. It will be concealed using sequentially numbered envelopes to be opened by a specified person in the team. As our psychologist will know who is having therapy (as supervisor) she will hold these envelopes.

Blinding

The graduate delivering the intervention in one group will assess the outcome of those in the opposite group blind to randomisation status. Outcome assessors will be blinded to randomisation status, but it will not be possible to blind study participants. The researchers will work separately, each assessing outcomes for approximately half the participants and providing therapy to those allocated to treatment in the half of participants they were not assessing. These teams will have supervision separately so as to remain blinded. Assessors will ask participants at the beginning of each interview not to disclose their allocation group. All assessments will take place in the home of the person with dementia or carer. We will require written consent according to the Mental Capacity Act (see details below)

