**Plan of investigation and timetable:**

Workpackage 1 (WP; 6 months)

01.02.16- 31.07.2016

-1 to 0 month: Place advert for psychology assistants with date of interview

0-1 month: Shortlist, interview and offer post, two RA to start June and one manager at the beginning of May if possible

0-6 months: Sponsorship, ethics and governance approvals, research passports applied for and put in place. The application for research ethics committee approval will be prepared by the CI and reviewed and signed by the sponsors (UCL) prior to submission. Local NHS Trust R&D site approvals and ethics committee approvals will be facilitated by CRN DeNDRoN.

0-6 months: Co-applicants develop manual using MRC framework for complex interventions, to incorporate existing evidence and qualitative interviews (family carers and people with dementia) about content, clarity, practicality and acceptability. We will also devise a training programme.

4-6 months: First RA joins in month 4 to help production of the final manual version; set up database for referrals; for assessments and separate password protected databases for each RA to keep data about intervention patients including adherence, time taken in phone calls and therapy and produce final case record forms.

4-6 months. Other two RAs join in month 6. Begin to train psychology graduates as research assistants (RA) and in the manual.

WP 2 (10 months) 01.08.2016- 31.05.2017

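### As described, the three-month service-use interview (CSRI) invites carers to reveal allocation to an assessor who is meant to stay blind

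*Protocol*

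**What the plan says.** Under Data collection, the CSRI is item 6 in the list headed "Patient: Baseline and three months", so it is given again after randomisation. Its stated purpose there is that it "will delineate treatment as usual (TAU) as well as treatment for those in the active arm of the study". The same section names the respondent: "We will collect all interview data from the carer to reduce patient burden", in an interview expected to last about 50 minutes.

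Under Assessment (Blinding): "Outcome assessors will be blinded to randomisation status, but it will not be possible to blind study participants". The protection within the interview is one sentence: "Assessors will ask participants at the beginning of each interview not to disclose their allocation group". That section also says that each researcher assesses about half of the participants and delivers therapy to those allocated to it in the other half.

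Two other places bear on the point. In the treatment-as-usual text under Health technologies being assessed, the CSRI is assigned only to describing usual treatment ("We will use the Client services Receipt Inventory"), and "participants randomised to the new treatment will also receive usual care". In the timetable for Workpackage 1, each research assistant has a separate database to "keep data about intervention patients including adherence, time taken in phone calls and therapy".

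**The concern.** One section gives a carer-answered instrument the task of describing what the active arm received. Another asks the same carer not to say which arm that was. If the person asking is the blinded assessor, the two instructions pull against each other.

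At stake is the blinding of the interviewer-administered measures. These include a side-effect record graded mild, moderate or severe, and scales collected because they are planned for the full trial. The Data collection section says that the study is meant to try out procedures for that trial, so an avoidable weakness in the blinded interview could be carried forward into it.

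**Working it through.** The plan gives no figure for unblinding, so the check sets the relevant statements side by side.

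1. **When.** The CSRI is taken at three months as well as at baseline, so allocation is known to the family when it is answered.
2. **Who answers.** The carer, who is not blinded.
3. **Who asks.** Not stated for the CSRI. All interview data come from a carer interview, and the three-month outcome interview belongs to the blinded assessor. The natural reading is therefore that the blinded assessor gives the CSRI. This is an inference.
4. **What it covers.** Data collection says usual treatment and also treatment in the active arm. The treatment-as-usual text mentions usual treatment only. The two descriptions differ, and neither says whether study sessions count.
5. **Wide reading of item 4.** If the CSRI records the study intervention, a complete answer from an active-arm carer states the allocation.
6. **Narrow reading of item 4.** If it records only usual services in both arms, the risk is smaller but remains. The protocol describes usual treatment as partly psychological, and lists cognitive stimulation therapy, carer support and, in some trusts, START. A carer asked about such services who has recently had manual-based sessions at home may well mention them, and no instruction says to leave them out. The assessor delivers the same intervention to other participants and could recognise even a loose description.
7. **What other safeguards exist.** The qualitative interviews about the intervention are placed after unblinding (Outcomes), so the protocol manages this risk there. Nothing comparable is stated for the CSRI.
8. **Which measures are exposed.** If list order were interview order, the Sleep Disorders Inventory, Neuropsychiatric Inventory, Epworth scale and DEMQOL proxy (items 1, 3, 4 and 5) would come before the CSRI (item 6). The safety and tolerability record (item 7) and the carer scales (PSQI, SCI, HADS, Zarit, HSQ) would come after it. The protocol does not say that list order is interview order, so another order could expose more or fewer measures.

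**What the numbers can and cannot show.** The inputs are 40 intervention and 20 control participants (Power calculation) and about 80% follow-up (same section). Equal follow-up in the two arms is an assumption.

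- Intervention interviews at three months: 0.80 × 40 = 32.
- Control interviews: 0.80 × 20 = 16.
- Intervention share: 32 / (32 + 16) = 32/48 = 67%, the same as 40/60.

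The 67% is the 2:1 allocation restated. It counts interviews in which there would be study sessions to mention, and it is not a rate of unblinding.

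**The case against.** The strongest reply is that the protocol nowhere says that the CSRI asks about DREAMS START sessions, and nowhere names who gives it. The active arm also receives usual care, so describing treatment in that arm can mean describing its usual services. The separate therapist databases support this reading, because intervention contacts already have a source. This stands against any claim that the blinded assessor must record study sessions or that the instrument by itself discloses allocation. It does not remove the invitation to disclose in step 6 of the working, because no text tells assessor or carer to leave study sessions out.

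Second, interview order is left to case record forms that are still to be produced. That is fair: the document fixes no order, and so no wrong one. It also means that the Sleep Disorders Inventory and Neuropsychiatric Inventory cannot be assumed to be affected.

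Third, the later measures are answered by an unblinded carer, and the carer scales are self-report, so the assessor's knowledge adds limited bias. This stands for the carer scales. It is weaker for the graded side-effect record.

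Fourth, some usual care may include START or other psychological support, so a mention of sessions need not identify the arm. This lowers the risk without removing it, given that assessors know the intervention's content.

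Fifth, the stop-go rule rests on adherence, the Data analysis section describes summaries and intervals with no efficacy test, and blinded assessment is not a listed objective. This limits the consequence. The stated intention to test procedures for a full trial keeps the point relevant.

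**Conclusion.** The concern holds in a limited form. The CSRI's stated purpose under Data collection is not reconciled with the blinding text under Assessment, the narrower purpose in the treatment-as-usual text, or the therapist databases in the timetable. On the natural reading, this creates an avoidable route to unblinding.

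The conclusion rests on one inference, that the blinded assessor gives the CSRI as part of the carer interview, and on the absence of any stated exclusion, order or separate interviewer. The primary outcomes (recruitment and adherence) and actigraphy do not depend on assessor judgement and are not affected.

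A reader might infer that the plan breaks its own blinding, with 32 of 48 or even all 48 interviews revealed. The documents do not support that. It would require the CSRI to ask about study sessions, every active-arm carer to report them despite the request not to disclose, and such a report always to identify the arm. None of these is stated. The point is worth correcting because the remedy is specific and cheap, but it does not threaten the study's main conclusions.

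**What to change.** Reconcile the CSRI entry under Data collection with the treatment-as-usual text, the Blinding text and the Workpackage 1 entry in the timetable:

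- Limit the assessor's CSRI to non-study services, with an explicit instruction not to ask about or record study sessions or study light equipment.
- Take DREAMS START contacts and time, for describing and costing the active arm, from the therapists' databases.
- Give the CSRI after all rated measures.
- Have assessors log any unblinding and the point in the interview at which it occurred. The study would then provide the estimate that the document cannot.

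The cost is a reordered case record form, a short log entry and a few lines of interviewer instruction. No new data source is needed.

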**Assessment**

*Procedures*

Referrals and recruitment procedure

Prospective eligible participants will be initially approached by a clinician they know and given (or sent) an information sheet or will volunteer through Join Dementia Research. Some prospective participants may have agreed to be contacted for research (as trusts may have a register) but we will still approach a clinician initially to ensure there have been no changes and ask, if possible, if they can make contact. Our experience is that this group of patients may not remember consenting and be very cautious of calls from strangers. Those interested in participating will be referred to the research team. The referral will give the name, sex and relationship of the patient and carer (this will allow testing for external validity by comparing the sample recruited with those who were referred but refused recruitment). The team that is to carry out blinded assessments will telephone them 24 hours or more after they receive the information sheet. They will answer any questions and then arrange to meet those who thought they wished to take part, to obtain their informed consent and complete the baseline assessment before randomisation.

Randomisation

We will use a randomisation list produced by the statistician. It will be concealed using sequentially numbered envelopes to be opened by a specified person in the team. As our psychologist will know who is having therapy (as supervisor) she will hold these envelopes.

Blinding

The graduate delivering the intervention in one group will assess the outcome of those in the opposite group blind to randomisation status. Outcome assessors will be blinded to randomisation status, but it will not be possible to blind study participants. The researchers will work separately, each assessing outcomes for approximately half the participants and providing therapy to those allocated to treatment in the half of participants they were not assessing. These teams will have supervision separately so as to remain blinded. Assessors will ask participants at the beginning of each interview not to disclose their allocation group. All assessments will take place in the home of the person with dementia or carer. We will require written consent according to the Mental Capacity Act (see details below)

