
Delivery The manual will be delivered individually, both because sleep disturbances are complex with causes and treatment differing between individuals; and as it can be difficult for family carers to attend a group which is only available at one particular time. We will emphasise, as in our previous work, a collaborative, non-prescriptive model, in which we encourage family carers to try techniques and note what works for them in their manual. We intend, as in our previous work, to deliver the intervention as a partnership of psychology graduates and family carers^10^. In practice, most people with dementia in the study will have carers with them at nights, as they will either be referred to services by their family, as causing disturbance to carers sleeping in the same house, or have night care as it is unsafe to leave them alone, but this will not be an inclusion or exclusion criterion. The research assistants will be a supervised psychology graduate, so that the manual can be rolled out using principles of training, supervision and stepped care. Psychology graduates will have a degree in psychology but without clinical psychology training and be recruited on evidence of listening skills, empathy and clinical experience. This level of expertise will ensure breadth of skills (to impart information, knowledge of dementia, mental health & knowing when more support is needed). The psychology graduate research assistants will all complete a specific but short training course, which we will document, to ensure a successful intervention is scalable and affordable, on dementia and sleep-wake regulation/sleep science. In addition, they will complete, UCL training in safety and diversity and training in Good Clinical Practice and informed consent. A short training programme will be delivered by our co-applicants. There will be a strong practical focus on how to deliver the intervention, develop empathic listening skills, make effective use of supervision and when to ask for help. They will also have teaching sessions dedicated to cultural sensitivity. Training will emphasise the need to operate from an inclusive values base and to respect diversity and the existing knowledge and experience of family carers and people with dementia. Knowledge will be acquired through a combination of seminars, discussion groups, reflective learning and guided reading. Skills-based competencies will be learnt through clinical simulation in small groups. In devising our training programme, we will draw on the curriculum for psychological therapists devised by the Department of Health for their improving access to psychological therapies programme (IAPT). All therapists will be trained to adhere to the manual. To ensure treatment integrity, they will be required to demonstrate by role-play, competence in delivering the intervention before recruitment commences. Therapists will, with the carer/patients’ permission, record a random intervention session. They will be supervised by a clinical psychologist (PR) and use recording in supervision. A researcher not involved in the therapy, who will independently rate fidelity to the manual using a standard checklist.

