**Data analysis:**

Randomised controlled trial

Our co-applicant statistician will lead and supervise the analysis. The statistical analyses will be described in a predefined statistical analysis plan, and planned and conducted according to ICH E9 and following the standard operating procedures of the PRIMENT clinical trials unit. A summary of the main analyses are given here.

Baseline data will be summarised by treatment group using means (with standard deviations), medians (with interquartile ranges), counts and proportions, as appropriate, to gauge the balance in characteristics between the randomised groups. A consort diagram will describe the flow of patients through the trial.

1. The proportion of participants in the intervention group that adhere to the treatment (attend a predetermined number of sessions) and the proportion of appropriate referrals consenting to the trial will be calculated with 95% confidence intervals.
2. Actigraph measurements of sleep efficiency (%), total sleep time (minutes) and wakefulness during the sleep period (minutes), the Epworth sleep inventory scores and the Sleep Disorders Inventory Scores will be summarised to provide distributional information and to obtain estimates of standard deviation and correlation needed for the sample size calculation of the main trial
3. Referral rates, drop out and loss to follow up rates will be calculated with 95% confidence intervals
4. In addition, prescription of psychotropic medication (to define rescue medication’s role) and co-morbid physical illnesses and patient falls will be summarised by randomised group.
5. Other patient and carer outcome data will also be summarised by randomised group using appropriate estimates with 95% confidence intervals.

Qualitative study

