**Project management**

The project will be sponsored by UCL and will require ethics and research and development approvals.

GL will have day to day management and control of the project and the project development group will meet at the beginning of the project and will outline the development of the manual and the tasks involved and meet weekly by teleconference or in person to ensure continued progress and milestones. The research assistants will have individual clinical supervision fortnightly by PR and will have the opportunity to consult GL, CC or PR in between as required. The co-applicants will comprise the Trial Management Group (TMG) and will meet three monthly throughout the project. There will be an independent Trial Steering Group (TSC) with PPI and IAPT service contribution. Trial Management and Steering Committees will ensure adherence to the Mental Capacity and Data Protection Acts; ethical guidelines and Information Governance procedures.

Central Monitoring

Each site to email the sponsor twice yearly:

1. Delegation log
2. Adverse Event log
3. Deviation Log
4. Minutes of trial Steering Committee (for equivalent)
5. Annual progress report (lead site only) when sent to Ethics Committee.

Information Governance

UCL processes the personal data of living individuals such as its research subjects in line with the Data Protection Act 1998 (DPA). The UK’s regulator for the DPA is the Information Commissioner’s Office. It is the duty of data controllers such as UCL to comply with the data protection principles with respect to personal data. All electronic data will be stored without name or address. Data will be held on a secure database on a password-protected UCL computer. Access to data will be restricted to the research team. To enable follow-up, it will be necessary to keep contact details for the participants, but this information will be restricted to key members of the team. Audio- recordings of interviews for training and fidelity monitoring (using a digital voice recorder) will be destroyed once the main study is complete. The digital recordings from the qualitative study and process evaluations will be destroyed when the study is completed.

Clinical Trials Regulations

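### The therapy supervisor holds the unopened allocation envelopes for a reason that covers only allocations already made: an avoidable weakness in concealment

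*Protocol*

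**What the plan says.** The Randomisation paragraph of the protocol's Assessment section fixes three things.

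- Source of the list: "We will use a randomisation list produced by the statistician".
- Concealment: "It will be concealed using sequentially numbered envelopes to be opened by a specified person in the team". That person is not identified.
- Custody: "As our psychologist will know who is having therapy (as supervisor) she will hold these envelopes".

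Other sections show what else the holder does.

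- Under Delivery (Health technologies being assessed), the protocol says of the therapists: "They will be supervised by a clinical psychologist". The initials given there also appear in the manual-development team, under Developing the intervention.
- Project management gives the same initials for the supervisor of the research assistants: "The research assistants will have individual clinical supervision fortnightly".
- The Assessment section and work package 2 of the timetable have the research assistants recruit, take consent and do the baseline assessments.

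The Assessment section also contains safeguards: consent and baseline are completed before randomisation, and the two research teams are supervised separately.

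**The concern.** Two questions are being run together. Who may know an allocation once it has been made is a matter of blinding, and a therapy supervisor has to know. Who keeps the allocations not yet made is a matter of concealment, and supervising therapy does not require that. The protocol answers the second question with a reason that fits only the first.

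The person chosen has a stake in the intervention and regular one-to-one contact with the staff who have met each patient and carer before allocation. Good concealment should not depend on the conduct of someone in that position, however trustworthy.

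Adherence is a primary outcome, is measured only in the intervention arm, and is what the stop-go bands are expressed in. If allocations were matched to pairs thought likely to attend, the adherence estimate would rise, and blinding the outcome assessor would not correct it.

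**Working it through.** **1. Does the stated reason reach the choice made?**

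| Need | Requires |
|---|---|
| Supervise therapists | Knowing who has been allocated to therapy, after allocation |
| Hold unopened envelopes | Custody of allocations not yet made |

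The first need is met in full if she is told each allocation after its release. Nothing in the protocol makes the second necessary.

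**2. What would steering need?** An envelope read early, used out of order, or matched to a chosen pair. Taking consent and baseline first limits selective enrolment as long as the contents stay unknown. It does not settle which of two consented pairs receives the next envelope, and the protocol expects about two participants to join per week. The text does not say whether the holder and the opener are the same person.

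**3. The plan's own figure.** Inputs from Power calculation: 40 intervention participants, 20 controls, expected adherence 75%, 95% CI 59-87%. The exact (Clopper-Pearson) interval for 30/40 is 58.8% to 87.3%, which reproduces it. There is no arithmetic error, and changing the holder alters neither the sample size nor the interval.

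**4. How sensitive is the rule?** The bands are 70% or more (go), 60-69% (modify) and below 60% (do not progress). One participant is 1/40 = 2.5 points.

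- 27/40 = 67.5% (modify); 28/40 = 70% (go).
- 23/40 = 57.5% (do not progress); 24/40 = 60% (modify).

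Let X be Binomial(40, p). Go requires X ≥ 28. If k certain non-adherers were exchanged for k certain adherers, go would require X ≥ 28 − k:

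| True adherence p | k = 0 | k = 1 | k = 2 |
|---|---|---|---|
| 60% | 0.13 | 0.21 | 0.32 |
| 65% | 0.31 | 0.44 | 0.57 |
| 75% (protocol's expectation) | 0.82 | 0.90 | 0.95 |

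**5. The same check with imperfect prediction.** Assume a pair with a 55% chance of adhering is exchanged for one with a 75% chance, all others being at 65%. P(go) then moves from 0.303 to 0.326 for one exchange (39 others) and from 0.291 to 0.338 for two (38 others). That is about 2 to 5 percentage points, against 13 (0.44 − 0.31) to 26 (0.57 − 0.31) in the 65% row above.

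The numbers of exchanges and the 55% and 75% values are assumptions; the documents give none. Both calculations show how the rule responds. Neither estimates bias in this trial.

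**The case against.** The strongest reply is that custody is not knowledge. The statistician makes the list, the envelopes conceal it and are numbered, and someone else may open them. The usual failure, a recruiter holding the envelopes, is avoided, and consent and baseline come first. All of this stands.

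Other stronger inferences should also be resisted.

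- A reader might infer that fortnightly supervision passes the holder details of pairs awaiting allocation. No section says that such pairs are discussed there.
- The protocol's remark that "we judge that many people will wish to be in the active plus TAU arm rather than the TAU arm" might be read as pressure on the holder. It describes participants' preferences, which would be voiced to the research assistants, who do not hold the envelopes.
- The larger shifts in P(go) might be read as expected bias. They assume perfect prediction of adherence, and any threshold on 40 people can turn on one of them, whoever holds the envelopes.
- Adherence might be read as the sole, binding determinant of progression. The protocol says only that it expects the stop-go measures to be related to it.
- The clinical trials unit might be taken as ready to run allocation. The phrase "following the standard operating procedures of the PRIMENT clinical trials unit" refers to the statistical analyses and shows no randomisation service.
- The absence of an opening log is silence; one may exist in working procedures not shown.

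The reply leaves one thing untouched: the reason given does not support the choice of holder.

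**Conclusion.** The point holds as a weakness of procedure that is easily avoided. The protocol places future allocations with the therapy supervisor, who also helps develop the manual and supervises those who recruit, and its justification covers only past allocations. A reader might infer that allocations will be steered, or that the adherence estimate is biased. The documents do not support either inference.

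The size of any effect cannot be derived from the documents. What can be said is that the go/modify boundary lies between 27 and 28 of 40, so a measure this sensitive deserves independent custody. Effects on the standard deviations or on drop-out in the usual-care arm are possible in principle but cannot be quantified here. The conclusion assumes that the matching initials denote one person throughout, as the text indicates.

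**What to change.** Replace the custody sentence in the Randomisation paragraph with wording to this effect: the list or envelopes are held by a named person with no role in recruitment, assessment, therapy or supervision; each allocation is released in sequence and logged with date and time, only after consent and baseline have been recorded under the participant's number; the psychologist is then told who is allocated to therapy. The holder could be the trial statistician's office, or the clinical trials unit if it offers this service.

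The cost is one changed sentence, about 60 logged releases (40 + 20 participants) and possibly a short delay between baseline and allocation. Sample size, confidence intervals, supervision and assessor blinding stay as they are. The change should be made before the first randomisation.
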